**Safety (all participants)**	
Adverse events	No serious adverse events or injuries that are possibly, probably, or definitely related to study participation.
**Feasibility and Acceptability—Research Procedures (all participants)**	
Recruitment rate	Average of 4–8 enrolled per month
MOSAIC Plus intervention procedures	80% of participants complete MOSAIC Plus intervention sessions at 3 months and 70% at 6-month follow-up
Timeliness of assessments	80% of follow-up assessments occur within 3-weeks of due date
Completeness of self-report instruments and interviews	Self-report instruments have 80% of items completed and interviews 90% of items completed in 90% of cases
Retention rate	80% complete 3-mo and 70% complete 6-mo follow up assessments
Participant burden	Qualitative responses from exit interviews do not suggest undue burden of intervention or research procedures

*2*.*2*.*8*.*1*. *Demographic/screening measures*. Will include age, educational level, marital status, occupation, employment (status, # hours per week), income, race, gestational age/age of children. At follow ups, occupation, employment (status, # hours per week), and income will be repeated. We will also assess relationship information, such as current relationship to the abuser/s and length of relationship. We will use the Composite Abuse Scale (CAS) [37] to include women who report any physical and sexual violence in the past six months. We will also use the Patient Health Questionnaire (PHQ-9) with a cut-off point of ≥ 9 [55] and/or the Davidson Trauma Scale (DTS) with a clinical cut off point of ≥ 40 to determine eligibility in terms of depressive and/or PTSD symptoms [39].

*2*.*2*.*8*.*2*. *Primary*: *Study Feasibility and Treatment Feasibility/Acceptability and safety*. We will assess feasibility of the research procedures by examining study recruitment and refusal rates, participants’ willingness to be randomized, follow-up rates, reliability and range of responses to study questionnaires. We will assess the feasibility and acceptability of MOSAIC Plus by examining treatment completion (based on the jointly established treatment plan) and drop-out. We will examine reasons for termination from study and/or intervention for consistent patterns. We will examine the acceptability of the MOSAIC Plus intervention by using data from CTQ-8 treatment satisfaction questionnaire, the End of Treatment Questionnaire, and detailed exit interviews. Clients’ experiences with the mentor mothers, the quality of their working relationship and their level of satisfaction with the service will be evaluated using the Working Alliance Inventory-Short Revised (WAI-SR). Moreover, as in the original MOSAIC study [34], we will also explore perspectives of the mentor mothers regarding acceptability of the MOSAIC Plus intervention. We will use Competency Assessment Inventory (CAI), which tests the attitudes, knowledge, and skills needed to provide high-quality mental health care (i.e., learns and respects clients’ preferences about intervention, creates opportunities for clients to practice skills).

At the end of the open trial and at 2 time-points during the RCT (i.e., after enrolling 20 and 40 participants), we will compute the descriptive data on all target outcomes described in Table 2. The scientific team will convene to discuss how our actual outcomes compare to target outcomes. If the team identifies discrepancies between target outcomes and actual outcomes, we will 1) investigate the reason for failure to meet the stated outcomes, and 2) discuss among the research team. Depending on the nature of the discrepancy, we may modify recruitment or assessment procedures, instructions to participants, training procedures, or other trial aspects. Table 1 below presents assessment methods.

**Table 2 pone.0267679.t002:** Target mechanisms.

Target Mechanism 1: Social support	
Definition	“Emotional, informational and practical assistance provided in a supportive social network” [69]
Evidence that adding IPT approaches increase social support	IPT has been found in many studies to increase social support relative to control conditions [70–73]
Evidence that increased social support reduces IPV and depressive and PTSD symptoms	• High social support is associated with lower depressive symptoms [53, 71, 74] • High social support is associated with lower PTSD symptoms, in general and after IPV [50, 75, 76] • Women with IPV who report high social support experience fewer depressive symptoms [46] • Social support protects women from the negative effects of IPV [45, 77]
**Target Mechanism 2: Effectiveness Obtaining Resources**	
Definition	• Women’s ability to access community resources such as legal, healthcare, housing, income assistance, education, jobs, etc. [63]
**Evidence that IPT increases effectiveness obtaining resources**	• IPT increases personal agency to access resources [78].
Evidence that effectiveness obtaining community resources reduces depressive symptoms, PTSD symptoms, and subsequent IPV	Access to community resources reduces subsequent IPV [79] Access to community resources reduces depressive symptoms [80] • Access to community resources reduces PTSD symptoms [81, 82]

#### 2.2.9. Clinical and services outcomes

*2*.*2*.*9*.*1*. *Mental health outcomes*. Reduction in depressive symptoms will be evaluated using the nine-item Patient Health Questionnaire (PHQ-9), a reliable self-report measure assessing the presence and severity of depressive symptoms [38]. We will measure changes in PTSD symptoms by using the 17 item Davidson Trauma Scale (DTS) [39], a reliable and well-validated self-report measure [56] of trauma assessing DSM-5 symptoms of PTSD rated on a five point frequency. We will use the DTS as a cross-sectional measure of PTSD symptoms in three domains including intrusion, avoidance/numbing and hyperarousal. Respondents will be asked to identify the most troubling traumatic experience in the past week and measure its severity and frequency in 5-point scales.

*2*.*2*.*9*.*2*. *IPV outcomes*. We will use the Composite Abuse Scale to measure victimization in the context of romantic and partner relationship for each intimate relationship over a specified period of time. The CAS has 4 dimensions including severe combined abuse, emotional abuse, physical abuse, and harassment.

*2*.*2*.*9*.*3*. *Functioning outcomes*. The 12-item WHO-Disability Assessment Schedule (WHO-DAS-II) [57] will be used to measure *functioning* in the domains of cognition, mobility, self-care, getting along/interaction with other people, life activities and participation in community activities. A nine-item assessment tool measuring Self-care and Self-worth will be used assess changes in self-care. The scale was developed based on our team’s previous qualitative work with high-risk women [58]. Items included “I take good care of myself,” “I need to take care of people around me before I take care of myself,” “I am worth taking care of,” “I am worth protecting,” “I deserve to be able to take care of myself,” “I deserve to protect myself,” “I neglect myself,” “I put myself in dangerous situations,” and “I take care of my needs,” and were answered on a 5-point Likert Scale from “Strongly agree” to “Strongly disagree.” The scale has an internal consistency reliability (Cronbach’s alpha) of .77. To measure *general health and wellbeing*, we will use SF-36 [59]. SF-36 has a good internal validity in research, community and clinical settings [59, 60].

*2*.*2*.*9*.*4*. *Target mechanisms*. We will measure *social support* using the RAND social support survey instrument (also known as Medical Outcome Study-Social Support Survey (MOS-SS) [61] that measures functional social support covering multiple dimensions including emotional/informational, tangible, affectionate and social interaction. The scale has previously been used in a study of maternal depression [62]. We will use the Effectiveness Obtaining Resources Scale (EOR) [63] to assess IPV exposed perinatal women’s’ effectiveness in obtaining resources from formal sources in 13 areas: housing, material, goods and services, education, employment, health care for themselves and their children, child care, transportation, social support, legal assistance, financial issues, and other issues regarding themselves and their children. The EOR was developed for use among women with IPV [63]. It is reliable, valid, and shows significant changes over time in clinical samples [63–65].

*2*.*2*.*9*.*5*. *Provider perspectives*. We will use Competency Assessment Inventory (CAI) to evaluate the skills, attitude and knowledge needed to deliver a high quality mentoring intervention [66]. We will also use the provider version of Working Alliance Inventory [67] to assess mentor mothers’ perceptions of agreement on mentorship goals, agreement on mentorship tasks, and the quality of the mentoring relationship with each participant mother.

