**Methods:**

This study will develop MOthers’ AdvocateS In the Community (MOSAIC) Plus intervention for pregnant women and mothers with children under the age of 5. MOSAIC uses trained mentor mothers and has been found to reduce subsequent IPV. This study will blend the original MOSAIC intervention with principles of interpersonal psychotherapy (IPT) to address symptoms of depression, PTSD, and prevent subsequent risk of IPV. We will conduct a pilot randomized trial of the MOSAIC Plus intervention compared to the traditional MOSAIC intervention to determine its feasibility and acceptability. Study samples include focus groups (n = 36), open trial (n = 15), and a randomized pilot trial including 40 pregnant women and mothers with children under 5 who report current/recent of IPV and elevated symptoms of maternal depression and/or PTSD. The study’s primary outcome will be changes in maternal depressive and PTSD symptoms. Secondary outcomes will include reduction in subsequent IPV, improvement in functioning, changes in social support and effectiveness in obtaining resources.

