### 2.2. Pilot study phase

In the **pilot study phase**, the MOSAIC Plus intervention will be compared to the traditional MOSAIC in 40 women. The goal of this phase will be to assess the feasibility of the research design, the acceptability of the MOSIAC Plus intervention and to explore 95% confidence intervals of reduction around depressive and PTSD symptoms, and decrease in the experience of IPV within a 9-month period from intake. The duration of both interventions will be 9 months. Study assessments will take place at baseline, 3, 6 and 9 months.

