#### 2.2.1. Sampling and recruitment

The randomized pilot study will involve 40 women who are 1) pregnant and/or are mothers of children under 5 and report IPV experiences in the past 6 months (as assessed by Composite Abuse Scale [37]) 2) aged 18 or above, and 3) have elevated depressive and/or PTSD symptoms (including full disorder). This will be determined using the Patient Health Questionnaire (PHQ-9) with a cutoff point of ≥9 [38], and the Davidson Trauma Scale (DTS) with a cut-off point of ≥40 [39]. We anticipate that the majority of study participants will have both elevated depressive and PTSD symptoms, given that 50% of individuals with PTSD also have comorbid major depressive disorders [40, 41], especially among women with IPV [21]. Participants will be excluded if they (1) cannot provide the name and contact information of at least two locator persons (~6%), and/or (2) do not have access to any telephone, (3) have a current serious mental illness requiring intensive care or (4) cannot understand English well enough to understand the consent form or assessment instruments when they are read aloud. Virtually all pregnant women and mothers of children under 5 accessing care in these settings speak English. An initial sample of 15 pregnant women and mothers with children under 5 will be recruited to participate in a nonrandomized open pilot trial and will receive the proposed MOSAIC Plus mentoring intervention. No woman will be excluded from recruitment on the basis of race, sexual orientation, gender identity? or disability status.

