#### 2.2.10. Data analysis

As this is an intervention development study, our primary goal is assessment of feasibility and acceptability of the MOSAIC Plus intervention and research procedures. However, pilot data can be used to demonstrate whether the effects of treatment look promising across a set of outcome variables, to begin to examine distribution of outcome variables to inform future analytic strategies, and to suggest, in concert with results from larger scale clinical trials in related fields, the range of effect sizes that would be reasonable to expect in a future trial. We will obtain the between treatment condition effect size estimates (with 95% CI) at each assessment (e.g., Cohen’s d or h) and the correlation between the same dependent variable at adjacent assessments. We will have complete data on approximately 40 participants (the minimum expected after participant loss due to attrition). Sample size guidelines for treatment development from Rounsaville et al. [68] recommend 15 to 30 participants per cell. Given that group means begin to stabilize by around 15, we believe a sample of 20 in each condition should provide some information relevant to demonstrating potential promise for MOSAIC Plus.

*2*.*2*.*10*.*1*. *Mental Health Outcomes*. We will: (1) Calculate the effect size and 95% CI for reduction in depressive symptoms (PHQ-9 scores). Exploratory tests for differences between conditions will use HLM, with baseline scores as a covariate. (2) Calculate the effect size and 95% CI separately for reduction in PTSD symptoms (DTS scores) using HLM with baseline DTS score as a covariate.

*2*.*2*.*10*.*2*. *IPV outcomes*. We will calculate the effect size and 95% CI separately for reduction in CAS scores using HLM with baseline CAS score as a covariate.

*2*.*2*.*10*.*3*. *Functioning outcomes*. For secondary outcomes, separate calculations of the effect sizes and 95% CI will be performed. These include improvement in functioning (WHODAS-12) self-care (Self-care and Self-worth scale) and general health and wellbeing (SF-36). Separate exploratory tests for differences between conditions will use HLM, with baseline scores as covariates.

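### As worded, 2.2.9.1 ties the PTSD scale's index trauma to the past week, which fits neither the 6-month IPV entry window nor a change score through 9 months

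*Protocol article*

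**What the plan says.** All references are to the protocol article.

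- **Use of the scale (2.2.9.1).** "We will measure changes in PTSD symptoms by using the 17 item Davidson Trauma Scale (DTS"), followed by "We will use the DTS as a cross-sectional measure of PTSD symptoms in three domains including intrusion, avoidance/numbing and hyperarousal". The instruction to respondents is then "Respondents will be asked to identify the most troubling traumatic experience in the past week and measure its severity and frequency in 5-point scales".
- **Entry (2.2.1, repeated in 2.2.8.1).** Women must "report IPV experiences in the past 6 months (as assessed by Composite Abuse Scale"). They must also have raised symptoms on the PHQ-9 (9 or more) and/or on "the Davidson Trauma Scale (DTS) with a cut-off point of ≥40".
- **Timing (2.2).** "Study assessments will take place at baseline, 3, 6 and 9 months".
- **Analysis (2.2.10.1).** "Calculate the effect size and 95% CI separately for reduction in PTSD symptoms (DTS scores) using HLM with baseline DTS score as a covariate".
- **Role.** The abstract states: "The study’s primary outcome will be changes in maternal depressive and PTSD symptoms". Section 2.2.10.4 also treats reduction in depressive and PTSD symptoms as the primary outcome. Sections 2.2.8 and 2.2.10 put feasibility and acceptability first and call the between-condition tests exploratory. Subsequent IPV is a separate outcome, measured by the CAS.

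No section names an index trauma, says whether it is carried from visit to visit, or says what is scored when no traumatic experience occurred in the past week.

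**The concern.** A PTSD score refers to symptoms linked to some traumatic experience. For a change score to mean symptom change, that experience should be the same at each visit. The instruction instead attaches the past week to the experience. Three consequences could follow if interviewers apply it as written:

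- A woman whose last violence was some weeks before an assessment may have no experience to rate at that visit, although her symptoms persist.
- A baseline score and a 9-month score may refer to different events, so adjusting for baseline DTS, and the correlation between adjacent assessments that 2.2.10 sets out to estimate, would link scores tied to different experiences.
- A score may rise or fall with whether violence recurred just before the visit. The DTS would then partly carry the IPV outcome.

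These effect sizes and correlations are what the pilot is meant to pass to a larger trial, and the mechanism analyses in 2.2.10.4 relate social support and access to resources to the same PTSD change.

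**Working it through.** The plan states no figure on this point, so there is nothing to reproduce. Three checks were made.

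**1. The past week against the entry window.** Inputs: 1 week (2.2.9.1) and 6 months, taken as 26 weeks (2.2.1).

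- Share of the window: 1/26 = 3.8%.
- Assume k IPV events fall independently and evenly over the 26 weeks. The chance of at least one in a given week is 1 − (25/26)^k.

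| k events in 26 weeks (assumed) | Chance of an event in the rated week |
|---|---|
| 1 | 4% |
| 6 | 21% |
| 12 | 38% |
| 26 | 64% |

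The document gives no event frequency, so the whole range of 4% to 64% remains open. Even at one event per week on average, 36% of women would have none in the rated week under this assumption.

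**2. Can the sentence be complete as it stands?** Inputs: 17 items and two 5-point scales (2.2.9.1), cut-off of 40 (2.2.1).

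- One experience rated once on two scales: maximum 2 × 4 = 8 (scored 0–4) or 2 × 5 = 10 (scored 1–5). Neither reaches 40.
- Seventeen symptoms rated on both scales: maximum 17 × 8 = 136 or 17 × 10 = 170. Both exceed 40.

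The ratings must therefore apply to the 17 symptoms, and the sentence leaves that out. This settles what is rated. It does not settle which experience the symptoms relate to.

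**3. How far could new violence alone move the DTS comparison?** Shift between arms = (DTS gap between women with and without a past-week event) × (difference between arms in the past-week event rate). All inputs are assumptions: gap 10 to 40 points, difference in rates 5 to 20 percentage points, SD 20 to 30.

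- Smallest: 10 × 0.05 = 0.5 points; 0.5/30 gives d = 0.02.
- Largest: 40 × 0.20 = 8 points; 8/20 gives d = 0.40.
- For comparison, the approximate 95% CI half-width for d with 20 per arm (2.2.10) is 1.96 × √(2/20) = 0.62.

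Both arms receive MOSAIC. A between-arm shift therefore needs the added IPT component to change recent violence, which 2.2.5.1 hypothesises through social support. A fall in violence common to both arms would affect within-arm DTS change but not the contrast.

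**The case against.** The strongest reply is that this is one compressed sentence about a named, cited scale in a journal article. The interviewer wording belongs to the questionnaire and the full protocol, which are not shown. Check 2 supports this in part: the literal sentence cannot describe the whole scale, so the authors probably had symptom ratings in mind. The past week can also be read with the word troubling, meaning the experience that troubled her most this week, whenever it happened. That reading removes the problem of having nothing to rate. It still allows a different experience to be named at each visit, so the change-score problem remains. The article does not merely omit a detail here; it states a rule, and the rule conflicts with its own design.

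A reader might infer more than the document supports:

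- *That the experience is chosen anew at each visit.* This is not stated. It is inferred from the cross-sectional label, the repeated assessments and the absence of a fixed index.
- *That the scale does not measure PTSD from the qualifying IPV.* It may do so: that violence may fall in the rated week or be the experience named. Nor does the protocol require symptoms to stem from that violence.
- *That women without a recent event cannot enter.* Entry is also open through PHQ-9 of 9 or more, and once the ratings apply to 17 symptoms, a DTS score of 40 is not ruled out.
- *That PTSD and IPV can no longer be separated.* IPV has its own instrument and its own analysis. The most that follows is partial overlap.

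It is also fair to say that the DTS contrast is exploratory in a pilot that 2.2.10 sizes at 20 per condition.

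**Conclusion.** The point holds as a defect in a stated measurement rule. The wording dates the index experience to the past week, which does not match the 6-month IPV criterion or the analysis of DTS change from baseline through 9 months, and nothing keeps the index experience constant. If the rule is applied as written, DTS change may mix symptom change with recent new violence.

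The size cannot be derived from the document. The 4% to 64% range and the d of 0.02 to 0.40 only show what the stated assumptions would give. Even the upper end lies inside the 0.62 half-width that the pilot would have around d. That limits the effect on any conclusion from this trial, but it does not make the estimates sound as inputs to the next one.

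Severity is moderate. Feasibility is the main goal and DTS tests are exploratory. Against that, the DTS is one of the two symptom routes to entry, and both the abstract and 2.2.10.4 call PTSD symptom change a primary outcome.

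**What to change.** Reword 2.2.9.1 to say that:

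1. the most troubling traumatic experience, whenever it occurred, is identified and recorded once at baseline;
2. the same experience is used at 3, 6 and 9 months;
3. the past week is the period over which the frequency and severity of the 17 symptoms are rated;
4. new violence between visits is left to the CAS.

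The index experience need not be restricted to IPV. If the questionnaire and full protocol already work this way, only the article's sentence needs correcting.

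The cost is a change to the interviewer instruction and one recorded field, with no added visits or items. It should be in place before baseline DTS scores are collected, because those scores decide entry and serve as the covariate. The downside is that distress tied only to a new event will not be captured on the DTS.

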#### 2.2.10. Data analysis

As this is an intervention development study, our primary goal is assessment of feasibility and acceptability of the MOSAIC Plus intervention and research procedures. However, pilot data can be used to demonstrate whether the effects of treatment look promising across a set of outcome variables, to begin to examine distribution of outcome variables to inform future analytic strategies, and to suggest, in concert with results from larger scale clinical trials in related fields, the range of effect sizes that would be reasonable to expect in a future trial. We will obtain the between treatment condition effect size estimates (with 95% CI) at each assessment (e.g., Cohen’s d or h) and the correlation between the same dependent variable at adjacent assessments. We will have complete data on approximately 40 participants (the minimum expected after participant loss due to attrition). Sample size guidelines for treatment development from Rounsaville et al. [68] recommend 15 to 30 participants per cell. Given that group means begin to stabilize by around 15, we believe a sample of 20 in each condition should provide some information relevant to demonstrating potential promise for MOSAIC Plus.

*2*.*2*.*10*.*1*. *Mental Health Outcomes*. We will: (1) Calculate the effect size and 95% CI for reduction in depressive symptoms (PHQ-9 scores). Exploratory tests for differences between conditions will use HLM, with baseline scores as a covariate. (2) Calculate the effect size and 95% CI separately for reduction in PTSD symptoms (DTS scores) using HLM with baseline DTS score as a covariate.

*2*.*2*.*10*.*2*. *IPV outcomes*. We will calculate the effect size and 95% CI separately for reduction in CAS scores using HLM with baseline CAS score as a covariate.

*2*.*2*.*10*.*3*. *Functioning outcomes*. For secondary outcomes, separate calculations of the effect sizes and 95% CI will be performed. These include improvement in functioning (WHODAS-12) self-care (Self-care and Self-worth scale) and general health and wellbeing (SF-36). Separate exploratory tests for differences between conditions will use HLM, with baseline scores as covariates.

*2*.*2*.*10*.*4*. *Target mechanisms*. We will separately calculate the effect size and 95% CI for the effect of the intervention on proposed target mechanisms including improved social support (measured using MOS-SS) and effectiveness obtaining resources (measured using EOR scale). Separate exploratory tests for differences between conditions will use HLM, with baseline scores as covariates. We will then explore the association of each of these target mechanisms with changes in our primary outcome (reduction in depressive and PTSD symptoms) from baseline through 9 months. These exploratory analyses will inform full tests of mediation (i.e., tests of the hypothesis that the effects of MOSAIC Plus on reduced depressive symptoms is mediated through improvement in social support and effectiveness obtaining resources) in a subsequent fully powered trial. Although we expect the MOSAIC Plus intervention show evidence of preliminary effectiveness, should the intervention show no or limited evidence, exploratory tests of target mechanisms will also provide some initial information about whether MOSAIC Plus’ limited effectiveness was due to failure to engage target mechanisms or to the target mechanisms not being associated with the final outcome. Target mechanisms are presented in Table 2 below.

*2*.*2*.*10*.*5*. *Personalization and processes*. We will explore marital status, maternal age, race/ethnicity, household income, parity, severity of IPV experience, gestational age at enrollment, and number of lifetime trauma experiences (as assessed by the Trauma History Questionnaire) [83] as predictors and moderators of treatment outcome. These variables were also used in the original MOSAIC study [24] and other studies with women with IPV experiences [25, 46, 84]. We expect that MOSAIC Plus will be appropriate for a full range of perinatal women with IPV experience. Preliminary analyses of dose-response effects will also be conducted.

*2*.*2*.*10*.*6*. *Treatment Integrity*. We will calculate scale reliabilities of adherence and competence ratings using both individual item correlations and total intraclass correlations. We will compute scale validity by correlating adherence and competence ratings to intervention outcomes, to each other, and to expert ([name]) ratings. Adherence and competence ratings of trained raters will be compared to expert global ratings to determine cut-off scores with sufficient sensitivity and specificity.

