#### 2.2.4. Randomization

Randomization to MOSAIC Plus or MOSAIC interventions will occur after the baseline assessment, in a 1:1 ratio. All baseline assessments are blind. Immediately after randomization, the research assistant will review the study outcome assessment schedule, means of contacting the research staff, and participants’ contacts with all participants. The study statistician will prepare the randomization schedule using opaque sealed envelopes before the enrollment of the first participant.

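### Section 2.2.10 gives 40 as the minimum with complete data after attrition, but 40 is also the number randomised, so the two agree only if no one is lost

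*Protocol article*

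**What the plan says.** The article fixes the size of the randomised pilot in several places.

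- Section 2.2: "the MOSAIC Plus intervention will be compared to the traditional MOSAIC in 40 women".
- Section 2.2.1: "The randomized pilot study will involve 40 women who are 1) pregnant" and/or mothers of young children.
- Section 2.2.4: allocation "will occur after the baseline assessment, in a 1:1 ratio", hence 20 per condition.
- Section 2.2.8.2: the two review points during the RCT fall "after enrolling 20 and 40 participants".

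Section 2.2.10 then states: "We will have complete data on approximately 40 participants (the minimum expected after participant loss due to attrition". The same paragraph cites a treatment-development guideline said to "recommend 15 to 30 participants per cell", adds that group means settle at around 15, and concludes that 20 per condition is enough to be informative.

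Table 1 (section 2.2.8), in the block on research procedures for all participants, sets the retention target: "80% complete 3-mo and 70% complete 6-mo follow up assessments". Assessments run to 9 months, but Table 1 gives no 9-month retention target.

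**The concern.** One number is given two incompatible roles. Forty is how many women enter the randomised comparison, and it is also the least number said to remain after losses. Both can be true only if nobody is lost. Yet the same article counts 70% retention at 6 months as a success.

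This paragraph holds the article's only sample-size rationale. Because the attrition sentence comes first, the 20 per condition reads as already net of loss, and the comparison with the guideline appears to have room to spare. The pilot's main quantitative output is a set of between-condition effect sizes with 95% CIs at each assessment, meant to inform a later trial. How precise those are depends on how many women are observed at each visit, not on how many were randomised.

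**Working it through.** **Inputs from the article**
- Randomised: N = 40, 1:1, so 20 per condition (sections 2.2, 2.2.1, 2.2.4).
- Retention targets: 80% at 3 months, 70% at 6 months, none at 9 months (Table 1).
- Guideline: 15 to 30 per cell (section 2.2.10).
- Stated complete-data figure: about 40 (section 2.2.10).

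**Input that is an assumption**
- d = 0.5, used only to illustrate CI width. The article states no effect size or precision.

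**Step 1. Can the stated figure be reproduced?** Completers = N × retention.
- 40 × 1.00 = 40: requires no loss at all.
- 40 × 0.95 = 38: about the loosest reading of *approximately 40*.
- 40 × 0.80 = 32: not 40.
- 40 × 0.70 = 28: not 40.

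If each woman is retained with probability 0.70, the chance of 38 or more completers out of 40 is about 0.0001, and the central 95% binomial range is 22 to 33.

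**Step 2. Numbers if the targets are only just met**
- 3 months: 40 × 0.80 = 32, or 16 per condition.
- 6 months: 40 × 0.70 = 28, or 14 per condition.

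**Step 3. Comparison with the guideline.** Fifteen per condition is 30 women, and 30/40 = 75% retention. At 70% the count is 14, one below the lower bound. At the 3-month target it is 16, one above.

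**Step 4. Precision of an unadjusted d.** SE(d) = √(2/n + d²/(4n)) with n per condition; half-width = 1.96 × SE. With d = 0.5:
- n = 20: √(0.1000 + 0.0031) = 0.321; half-width 0.63.
- n = 16: √(0.1250 + 0.0039) = 0.359; half-width 0.70.
- n = 14: √(0.1429 + 0.0045) = 0.384; half-width 0.75.

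From 20 to 14 per condition the interval widens by 0.752/0.629 = 1.20, about 20%. The choice of d hardly matters: at d = 0 the half-widths are 0.62 and 0.74.

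**Step 5. The reverse reading.** If 40 completers were intended, enrolment would have to be 40/0.70 = 57.1, so 58 (29 per condition), or 40/0.80 = 50 at the 3-month target. Neither number appears in the article.

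**Step 6. Could the open-trial women make up the number?** (40 + 15) × 0.70 = 38.5, which is close to 40. But those 15 are not randomised, all receive MOSAIC Plus, and the paragraph goes on to speak of 20 in each condition. They cannot supply the control arm.

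**The case against.** The strongest case on the other side accepts that the sentence is wrong and disputes how much follows from it. Most of that case stands, and it limits the point.

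- **A reader might infer that the trial should expect 28 completers.** The article does not say so. The 80% and 70% figures are feasibility pass marks; missing them leads to team discussion and possible procedural changes. Twenty-eight is the number if the 6-month mark is only just met, and better retention gives more.
- **A reader might carry the loss forward to 9 months.** Continuing at the 3-to-6-month pace would give 60%, or 24 women. No source in the article supports this, because no 9-month target is given.
- **A reader might say the sample-size rationale collapses.** The shortfall at the pass mark is one woman per condition. The guideline as cited refers to participants per cell and does not specify completers, so 20 randomised per condition meets it. The conclusion the article draws from it is also modest.
- **A reader might say the intervals will be wider than the plan claims.** The plan claims no width. The half-widths above fit the unadjusted per-assessment effect sizes. They do not describe the HLM analyses with a baseline covariate, which may use partial follow-up.
- **A reader might conclude that enrolment is too small.** The article does not settle whether 40 completers were ever intended. The repeated statements of 40 randomised, and review points that stop at 40 enrolled, favour a slip in the attrition sentence.

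None of this rescues the sentence itself. It speaks of complete data, so partial follow-up in an HLM does not help. It calls 40 a minimum, when 40 is the maximum.

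**Conclusion.** The point holds as an internal contradiction with a wrong figure. Section 2.2.10 uses 40 both as the number randomised and as the post-attrition minimum, which is impossible with any loss and conflicts with the Table 1 retention targets. At those targets the numbers are 32 (16 per condition) at 3 months and 28 (14 per condition) at 6 months. The 15-per-cell guideline is met by the number randomised but not necessarily by completers.

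The counts rest on the targets being exactly met and on equal loss in the two conditions. The half-widths (0.75 against 0.63) rest in addition on an unadjusted d and an assumed d of 0.5.

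Severity is moderate. The aim is feasibility and acceptability, between-condition tests are exploratory, the article says it is underpowered, and there is no power calculation to invalidate. The documents do not support reading this as a forecast of 30% loss or as proof that more women must be enrolled.

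**What to change.** Rewrite the attrition sentence in section 2.2.10 along these lines:

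- Forty women are randomised, 20 per condition. If the Table 1 retention targets are only just met, about 32 (16 per condition) will be assessed at 3 months and about 28 (14 per condition) at 6 months.
- The 15-to-30-per-cell guideline is met by the number randomised. At 70% retention completers fall slightly below it; 75% is needed for 15 per condition.
- Base any statement of expected precision on these numbers. For an unadjusted d, with d = 0.5 as an assumed value, the 95% CI half-width is about 0.75 at 14 per condition against 0.63 at 20.
- Add a 9-month retention target to Table 1, or label any 9-month number as an assumption.

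If the investigators did intend 40 completers, the enrolment figure is the one to reconcile: about 58 randomised at 70% retention. Restating the figure is the cheap route. It changes a few sentences and gives a less favourable number, with no change to enrolment, allocation, outcomes or analyses.
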